DOR is a heterogeneous disorder with diverse clinical manifestations that not only impair fertility but also cause menstrual irregularities and perimenopausal symptoms (e.g., insomnia, anxiety, depression, and cognitive dysfunction) (9). Compelling evidence reveals a bidirectional relationship between DOR and psychological distress - approximately 50% of DOR patients exhibit significant depressive symptoms, anxiety, and emotional dysregulation, which may exacerbate DOR progression through hypothalamic-pituitary-gonadal axis dysfunction (10). This neuroendocrine-psychological interplay underscores the mutual reinforcement between DOR and mood disorders, with potential central nervous system consequences. Previous studies have suggested that abnormalities in the hypothalamic-pituitary-ovarian (HPO) axis may be a potential underlying cause of DOR (11). Dysregulation at any point of this axis, whether at the hypothalamic, pituitary, or ovarian level, can disrupt the normal hormonal signaling required for optimal ovarian function, leading to a reduction in the quantity and quality of oocytes (12). Such dysfunction may result from various factors, including endocrine disorders, genetic predispositions, or environmental influences, which can ultimately contribute to the pathogenesis of DOR (13). HPO axis is critical for the maintenance of mental and physical health (14). Understanding these disruptions in the HPO axis may offer new insights into the mechanisms driving DOR and pave the way for more effective diagnostic and therapeutic approaches. In recent decades, the advent of noninvasive functional magnetic resonance imaging (fMRI) has provided unprecedented insights into brain activity, enabling the exploration of central physiological processes with remarkable precision. This advanced imaging technique has revolutionized our ability to investigate the dynamic neural mechanisms underlying a wide range of mental, physical, and emotional functions, thus significantly enhancing our understanding of brain function in both health and disease (15–17).

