DOR patients might suffer from chronic estrogen deficiency, hormone replacement therapy (HRT) is one of the most widely used treatment (18). This treatment approach seeks to relieve symptoms and restore hormone levels to a physiologically normal range, but it also comes with potential drawbacks, such as increase the risk of ovarian cancer (19). Platelet-rich plasma (PRP) is another promising treatment that has shown the potential to promote endometrial and follicle growth for restoring female reproductive and endocrine function, while the results shows that it do not improve IVF outcomes in women under 38 and lack of standardization (20, 21). Given this context, there is an urgent need for an effective treatment for DOR. Acupuncture is a traditional Chinese medical (TCM) approach involves treating patients by stimulating specific acupoints on the body to regulate the flow of Qi and blood within the meridian system. For decades, acupuncture has found extensive application in the treatment of a diverse array of physical or mental diseases, encompassing conditions like infertility, ovarian insufficiency, menstrual cycle irregularity, insomnia, and depression (6, 22–24). Acupuncture has been widely used to treat DOR, and has demonstrated curative effects (25, 26). Also, acupuncture could modulate homeostasis of HPO axis (27). However, due to a lack of high-quality evidence supporting its use and insufficient elucidation on the mechanisms underlying acupuncture’s effects.

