### Participants

We plan to recruit 42 patients with DOR and 21 healthy female volunteers of childbearing age through WeChat, poster postings, and other channels. A dedicated staff member will be responsible for patient recruitment and will meticulously record each participant’s information, which will be documented in the Case Report Form (CRF). The recruitment materials will include detailed contact information. This study adheres to the principles outlined in the Declaration of Helsinki.

Inclusion criteria for healthy controls:

Age between 20 and 40 years (inclusive).Normal gynecological ultrasound, normal hormone levels, and regular menstrual flow with normal color and quantity.No severe heart, liver, kidney, or hematologic system disorders.Right-handed.Voluntary participation in the trial and signed informed consent.

The inclusion criteria for DOR are similar to our previous design (23):

Age between 20 and 40 years (inclusive).Diagnosis of DOR based on the 2016 POSEIDON criteria and the 2020 expert consensus on the treatment of low-prognosis populations in assisted reproductive technology using the Delphi method in China.AMH level < 1.2 ng/ml.AFC < 5 (Note: AFC should be measured on days 2–3 of the menstrual cycle, with at least a 4-week interval between two measurements).Fertility desire, with plans for natural conception or, as assessed by a reproductive specialist, plans to undergo controlled ovarian stimulation with an antagonist protocol in the next *in vitro* fertilization (IVF) and embryo transfer cycle.Right-handed.Voluntary participation in the trial and signed informed consent.

Exclusion criteria:

Coexisting conditions that affect fertility, including congenital reproductive organ abnormalities, untreated endometrial polyps, untreated uterine infections, untreated tubal hydrosalpinx, thin endometrium, uterine fibroids, endometriosis, or other organic diseases.Coexisting polycystic ovary syndrome (PCOS).Coexisting untreated hyperprolactinemia, hyperandrogenism, thyroid dysfunction, chronic adrenal insufficiency, or other metabolic and endocrine disorders.Acupuncture treatment for fertility enhancement received within the last three months.Plans for *in vitro* fertilization (IVF-ET) within 2 months after enrollment.Vulnerable populations other than illiterate individuals, including those with mental illness, cognitive impairments, critically ill patients, pregnant women, etc.

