LR3	On the dorsum of the foot, between the first and second metatarsal bones, in the depression distal to the junction of the bases of the two bones, over the dorsalis pedis artery	90° [obliquely towards Yongquan (KI1)]	10–20 mm
BL23	In the lumbar region, at the same level as the inferior border of the spinous process of the second lumbar vertebra(L2),1.5 B-cun lateral to the posterior median line	90°	30–40 mm
BL33	In the sacral region, in the third posterior sacral foramen	90°	60–70 mm
KI3	On the posteromedial aspect of the ankle, in the depression between the prominence of the medial malleolus and the calcaneal tendon	90°	30–40 mm

The patients were asked to lie on their backs or stomach (depends on group A or B) in a quiet position, exposed to acupuncture. For VA group, after 75% alcohol disinfection, the Hwato^®^ (Huatuo brand made in Suzhou Medical Appliance Factory, Jiangsu, China) disposable needle (Φ=0.25*25 mm, Φ=0.25*40 mm, Φ=0.30*75 mm) is used in conjunction with the Park Sham Acupuncture Device (PSD, DongBang acupuncture company) (30). Expose the tip of the needle, apply a suitable needle insertion method, and attach the park device to the skin. Depending on the muscular layer depth of the acupuncture points, we adjusted the needle insertion depth until the patient experienced the “deqi” sensation. Needle manipulation techniques such as lifting, thrusting or twirling will be applied to promote ‘deqi’ (a sensation experienced by patients at the acupoint location, characterized by soreness, numbness, heaviness, and distention, etc). Acupuncture needles for VA will be inserted perpendicularly into a depth of 10–20 mm for GV20, GV24 and GB13, obliquely towards Yongquan (KI1) into a depth of 10–20 mm for LR3, deeply into a depth of 60–70 mm into the third posterior sacral foramina for BL33, and perpendicularly into a depth of 30–40 mm for the remaining acupoints. Needle retention time will last for 20 min per session, once every other day, 3 sessions a week for 12 weeks, totaling 36 treatment sessions.

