The SA group will receive a non-inserted acupuncture using the sham needle supported by the PSD. This needle has a retractable needle shaft and a blunt tip, they could not penetrate the skin (33). We gently placed the sham needle and PSD on the skin. The sham needle is then left no more manipulated to avoid any further physiological effects, thereby minimizing the potential for additional effects (34). The acupoints is same to the VA group. At the end of the treatment, the acupuncturist also used a dry cotton ball to press the acupoints so that patients could feel the withdrawal of ‘real’ needles (35).

At the conclusion of the trial, all participants were asked to complete a blinding assessment questionnaire containing the following question: “Which group do you believe you were assigned to during the study?” The response options were: A) VA (treatment group), B) SA (control group), or C) Uncertain. This assessment served three primary purposes: First, to quantify blinding efficacy by calculating the percentage of correct versus incorrect guesses. Second, to validate whether the sham acupuncture procedures had successfully masked group allocation. Finally, to assess any potential bias in self-reported outcomes, particularly for psychological scales.

During the trial period, all participants were explicitly instructed to refrain from any additional interventions, including moxibustion, cupping, and herbal remedies, that could potentially influence the study outcomes.

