### Clinical outcome measurement

The AFC will be measured via transvaginal ultrasonography on days 2–5 of the menstrual cycle. AFC, along with serum levels of basal FSH and AMH, will be assessed at three time points: baseline (week 0), post-treatment (week 12), and 12-week follow-up (week 24).

The neuro-psychological test such as SAS, SDS, and SRSS will be used for clinical assessments at three time points: baseline (week 0), post-treatment (week 12), and 12-week follow-up (week 24).

The time points for each test in two group is listed in **Table 2**.

**Table 2 T2:** Time points for each test in two groups .

Measurements	Baseline		12 weeks		24 weeks	
	DOR	HC	DOR	HC	DOR	HC
AFC, FSH, AMH	✓	✓	✓		✓	
AFC	✓		✓			
SAS, SDS, and SRSS	✓	✓	✓		✓	
MRI	✓	✓	✓			

Diminished ovarian reserve, DOR; healthy control, HC; anti-Müllerian hormone, AMH; antral follicle count, AFC; follicle-stimulating hormone, FSH; self-rating anxiety scale, SAS; self-rating depression scale, SDS; self-rating scale of sleep, SRSS; magnetic resonance imaging, fMRI.

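### The three-month acupuncture washout covers only fertility acupuncture, so women recently needled for insomnia, subclinical mood symptoms or other reasons can enter with treated baselines

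*Protocol article*

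**What the plan says.** The exclusion list in the Protocol article, Participants, contains one criterion on earlier acupuncture: "Acupuncture treatment for fertility enhancement received within the last three months". No other section restricts acupuncture for another reason before enrolment, and none requires women who have never been needled. The list follows the inclusion criteria for both controls and patients and is not assigned to either group.

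Other parts of the article bear on the scope of that criterion:

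- The Introduction says acupuncture is applied to "conditions like infertility, ovarian insufficiency, menstrual cycle irregularity, insomnia, and depression".
- The Introduction also says that DOR can "cause menstrual irregularities and perimenopausal symptoms (e.g., insomnia, anxiety, depression, and cognitive dysfunction".
- Under Clinical outcome measurement, "The neuro-psychological test such as SAS, SDS, and SRSS will be used for clinical assessments at three time points". All three scales are self-rated.
- The Introduction avoids a penetrating sham because it may affect brain function and confound the results. The Discussion cites connectivity changes in depressed patients after needling at GV20, which is one of the trial's own points.
- Under Acupuncture interventions, verum needles penetrate: "Needle manipulation techniques such as lifting, thrusting or twirling will be applied to promote" the deqi sensation. Of the sham: "This needle has a retractable needle shaft and a blunt tip, they could not penetrate the skin". It is also left unmanipulated.
- Randomisation is stratified by age only, and the sample size is 21 per group.

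**The concern.** The criterion has a sensible window but limits it by indication. By the article's own account, sleep and mood complaints are common in DOR, are treated with acupuncture, and are what SAS, SDS and SRSS measure. It also treats real needling as able to change the imaging outcome. A woman needled for insomnia up to the week before her baseline scan nevertheless meets every stated criterion.

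Two consequences follow. First, her baseline may already be partly treated. That matters for each analysis that takes the DOR baseline at face value: DOR against healthy controls, the paired before-after tests in each arm, the conjunction of the DOR map with the treatment maps, and the correlation of connectivity change with clinical improvement in the verum arm. These analyses are central to a mechanistic study. Second, recent experience of penetration and deqi gives her something to compare the sham with, and this could reach the self-rated verum-sham comparison.

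**Working it through.** **No figure in the plan to reproduce.** The point concerns eligibility wording. The 21 per group rests on precedent from earlier fMRI studies, without an effect size, SD or power. The article does not give the share of women with recent non-fertility acupuncture, the size of any residual effect, or the rate of sham recognition. All three are assumed below.

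**Assumptions.** Exposed share f = 0.10 to 0.30. Residual shift in an exposed woman's baseline c = 0.3 to 0.5 SD. Probability that an exposed woman in the sham arm recognises the sham r = 0.2 to 0.4. Worsening of her self-rating if she does, δ = 0.5 SD.

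**1. Carry-over in the DOR baseline mean.** Shift = f × c.
- Low: 0.10 × 0.3 = 0.03 SD.
- High: 0.30 × 0.5 = 0.15 SD.

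For scale, the standard error of a DOR-control difference with 42 and 21 women is √(1/42 + 1/21) = 0.27 SD. The shift is a bias that analysis cannot remove if exposure was never recorded, but it is smaller than one standard error.

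**2. Within-arm change.** If verum treatment simply replaces the earlier effect, the verum arm's mean improvement is understated by the same f × c. If the earlier effect fades under sham, the sham arm shows a spurious worsening of up to f × c. The range is again 0.03 to 0.15 SD.

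**3. Verum against sham: carry-over.** Exposure precedes randomisation, so its expected share is equal in the two arms and the expected bias is zero. Chance imbalance remains. At f = 0.20 the SD of the difference in exposed share is √(2 × 0.2 × 0.8 / 21) = 0.123. With c = 0.5 this is 0.123 × 0.5 = 0.06 SD, against a standard error of √(2/21) = 0.31 SD for the two-arm difference. With 8 of 42 women exposed, the chance that the arms differ by at least 4 such women is 24% (hypergeometric, simple equal-size allocation). This is part of ordinary sampling error.

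**4. Verum against sham: recognition.** Only exposed women in the sham arm can add recognition because of this gap. Bias = f × r × δ.
- Low: 0.10 × 0.2 × 0.5 = 0.01 SD.
- High: 0.30 × 0.4 × 0.5 = 0.06 SD.
- Ceiling, if every exposed woman recognised the sham (r = 1): 0.10 × 0.5 = 0.05 to 0.30 × 0.5 = 0.15 SD.

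Recognition that would have occurred without recent needling should be subtracted from these values.

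**The case against.** The strongest reply is that the consequence is permitted, not documented, and probably small. Much of it stands.

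- **Who is exposed.** Every patient must have a fertility desire, and the point set is named for both fertility and menstrual regulation. Recent menstrual acupuncture may therefore already be read as fertility treatment and excluded. The mental-illness exclusion removes some women treated for mood. The clear remaining cases are insomnia, subclinical mood symptoms and unrelated indications, and no criterion covers these.
- **The randomised contrast.** A reader might infer that treated baselines bias verum against sham. They do not on average, and the chance imbalance is small beside the standard error.
- **Masking.** A reader might apply 20–40% recognition to the whole sham arm and conclude that self-rated differences are inflated by 0.1–0.2 SD. That charges the general credibility of the sham to one eligibility phrase; only recently needled women count here. The plan also uses the Park device in both arms, separate rooms, cotton-ball pressure at withdrawal and an end-of-trial guess questionnaire. None of these screens for recent needling, and the questionnaire can detect unmasking but not prevent it.
- **Other therapies.** A reader might extend the point to the instruction to "refrain from any additional interventions, including moxibustion, cupping, and herbal remedies", which applies during the trial, and object that no window before enrolment is given. That rests on silence in a condensed article whose full protocol is not shown, so it is not part of this point. The acupuncture criterion differs because its scope is stated.

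**Conclusion.** The point holds in limited form. The stated washout is restricted by indication and leaves eligible some women whose recent needling could, on the article's own reasoning, alter both baseline connectivity and the sleep and mood scores. The exposed analyses are DOR against controls, the within-arm paired tests, the conjunction analysis and the verum-arm correlation.

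Under assumed exposure of 10–30% and a shift of 0.3–0.5 SD, the DOR baseline mean moves by about 0.03–0.15 SD. Added sham recognition contributes about 0.01–0.06 SD on the self-rated scales, and at most 0.15 SD. AMH, FSH and AFC are less open to recognition of the sham. The gap itself is certain from the text; its size is not, because every exposure, effect and recognition value is assumed. It is a cheap improvement to the design and does not invalidate the randomised comparison.

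**What to change.** Reword the exclusion to: Acupuncture for any indication within the last three months. State that it applies to both DOR patients and healthy controls. Record prior acupuncture experience, including experience before the three-month window, at screening, and tabulate the existing blinding-questionnaire guesses by it.

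The reworded criterion addresses carry-over. It only partly addresses recognition of the sham, because memory of real needling can outlast three months. The screening record and the tabulation would show whether experienced women guess their arm more often, but would not prevent it.

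The cost is one amended criterion, one screening question and one table, with a few extra screen failures or delayed starts.

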### fMRI data acquisition

All DOR patients received two separate resting-state fMRI scanning, before and after the 12 weeks acupuncture treatment course, respectively. The healthy controls participated only in one resting-state scanning as baseline control. For all participants, fMRI scanning should be done at least 3 day away from their menstrual period.

In this study, 3.0 T MRI scanner (Siemens, Sonata, Germany) at the Sir Run Shaw Hospital, was used to perform cranial scans on all subjects. (1) T1-weighted imaging (T1WI): horizontal axis position, TR = 600 ms, TE = 10 ms, slice thickness = 4 mm, slice gap = 1.5 mm, field-of-view (FOV) = 240 mm × 240 mm, matrix = 256×256. (2) Resting-state fMRI sequence and parameters: acquired with gradient echo-echo planar imaging (GRE-EPI) sequence, TR = 2000 ms, TE = 30 ms, slice thickness = 4 mm, slice gap = 1.2 mm, FOV = 220 mm × 220 mm, matrix = 64 × 64, flip angle = 90°, 200 time points in total, 35 slices scanned continuously. The entire brain will be scanned, and during the procedure, participants will be instructed to lie supine with their eyes open, while being asked to refrain from focusing on any specific thoughts.

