The hypothalamus functions as the central command center of the neuroendocrine system, with the HPO axis serving as the dominant regulatory pathway for female reproductive function. This axis precisely controls follicular development and steroid hormone production through gonadotropin-releasing hormone (GnRH)-mediated pulsatile secretion of follicle-stimulating hormone (FSH) and LH (47). Emerging evidence indicates that HPO axis dysregulation, a characteristic feature of diminished ovarian reserve (DOR), manifests not only as reproductive dysfunction but also involves extensive neural network alterations encompassing cortical and limbic systems, reflecting its unique neuro-reproductive integration. At the molecular level, the kisspeptin/GPR54 signaling system acts as the key upstream regulator of GnRH neurons, with anatomically and functionally distinct populations in the anteroventral periventricular nucleus (AVPV) and arcuate nucleus (ARC) mediating estrogen’s positive and negative feedback effects, respectively (48). Importantly, chronic stress-induced activation of the hypothalamic-pituitary-adrenal (HPA) axis leads to sustained glucocorticoid elevation, which directly suppresses GnRH pulsatility and consequently disrupts HPO axis function, establishing a critical pathway through which psychological stress impacts reproductive health (49). In this study, we will use fMRI to analyze hypothalamus and further more in periventricular nucleus such as AVPV and ARC.

This study adopts an interdisciplinary approach (integrating acupuncture, neuroimaging, and gynecology) to elucidate the central neural mechanisms of acupuncture in improving DOR, establishing a paradigm for modernizing research on traditional therapies. Using fMRI, we systematically investigate how acupuncture modulates functional connectivity in the hypothalamic network of DOR patients, innovatively revealing potential neural targets underlying acupuncture’s therapeutic effects. Through multidimensional assessments—including ovarian reserve markers (AMH/AFC/FSH), psychological scales (SAS/SDS/SRSS), and neuroimaging data—we demonstrate the synergistic improvement of acupuncture on reproductive, psychological, and neurological functions. Technically, the study employs the Park Sham Device to standardize sham acupuncture procedures, ensuring rigorous experimental design.

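### The 2-month IVF exclusion ends at least 22–25 days before the week-12 markers and second hypothalamic scan, and ovarian stimulation is not named among the barred interventions

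*Protocol article*

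**What the plan says.** All references are to the protocol article.

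- **Participants, inclusion criteria for DOR.** One criterion reads "Fertility desire, with plans for natural conception or, as assessed by a reproductive specialist, plans to undergo controlled ovarian stimulation". This refers to the woman's next IVF cycle, using an antagonist protocol, and no date is set for that cycle.
- **Participants, exclusion criteria.** Women are excluded if they have plans for in vitro "fertilization (IVF-ET) within 2 months after enrollment".
- **Participants, forced termination.** The events that end the intervention are serious illness, pregnancy and withdrawal of consent. Starting IVF or stimulation is not among them.
- **Acupuncture interventions.** The course is "3 sessions a week for 12 weeks, totaling 36 treatment sessions". On concomitant treatment: "During the trial period, all participants were explicitly instructed to refrain from any additional interventions, including moxibustion, cupping, and herbal remedies", where these could affect the outcomes.
- **Clinical outcome measurement.** "AFC, along with serum levels of basal FSH and AMH, will be assessed at three time points": weeks 0, 12 and 24. AFC is tied to cycle days 2–5.
- **fMRI data acquisition.** "All DOR patients received two separate resting-state fMRI scanning, before and after the 12 weeks acupuncture treatment course". The only timing rule is that "fMRI scanning should be done at least 3 day away from their menstrual period".
- **Discussion.** The stated target is hypothalamic: "we will use fMRI to analyze hypothalamus and further more in periventricular nucleus such as AVPV and ARC". The same paragraph describes these two nuclei as mediating estrogen feedback.

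**The concern.** The entry limit on IVF appears to be set without regard to the trial's own schedule. A woman who plans to start stimulation in weeks 9–12 meets every written criterion, and she belongs to a group that the trial expressly recruits. Her post-treatment assessments could then fall in or after a stimulated cycle.

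The scan is the most exposed outcome. It measures hypothalamic connectivity, and ovarian stimulation acts on the same hormonal axis. The timing rule keeps the scan away from menstruation but not out of a stimulated cycle. A change in connectivity at week 12 could then reflect the stimulation rather than acupuncture, and it would carry over into the planned correlations between connectivity change and clinical improvement. With 21 women per arm, each affected scan is 1/21, or about 5%, of an arm.

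Two of the ovarian markers are partly protected, because AFC is tied to early cycle days and FSH must be basal. For these the likelier result is a missing or rescheduled value.

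**Working it through.** **Inputs**

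| Quantity | Value | Source |
|---|---|---|
| IVF exclusion, from enrollment | 2 months | Participants, exclusion criteria |
| Treatment course | 12 weeks, 3 sessions a week | Acupuncture interventions |
| Marker assessments | weeks 0, 12, 24 | Clinical outcome measurement |
| Second scan | after the 12-week course | fMRI data acquisition |
| Wait from enrollment to first session | not given; 0, 7, 14, 28 days assumed | assumption |

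**Step 1: the plan's own figure.** 3 × 12 = 36 sessions, which agrees with the stated total. The course lasts 12 × 7 = 84 days.

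**Step 2: length of the exclusion.** Two calendar months, computed for every start date from 2025 to 2028, are 59 to 62 days.

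**Step 3: gap to week 12.** With wait *w* from enrollment to the first session, gap = 84 + *w* − 62 to 84 + *w* − 59.

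| Assumed wait *w* (days) | Gap to week 12 (days) |
|---|---|
| 0 | 22–25 |
| 7 | 29–32 |
| 14 | 36–39 |
| 28 | 50–53 |

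The first row is the minimum: treatment cannot start before enrollment, and the second scan cannot precede the end of the course.

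**Step 4: treatment left uncovered.** With *w* = 0, the sessions after the limit number 3 × 22/7 = 9.4 to 3 × 25/7 = 10.7, so about 9–11 of the 36.

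**Step 5: gap to week 24.** 168 − 62 = 106 to 168 − 59 = 109 days, again with *w* = 0.

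**Step 6: does another rule close the gap?** Set side by side:

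- *The instruction on additional interventions.* Its wording is general, but every named example is a complementary therapy. If it does bar IVF throughout, the entry criterion admits women whose month-3 IVF plans the trial then forbids. If it does not, the gap is open. The 2-month limit is mis-set on either reading.
- *The termination events.* Starting IVF is not listed.
- *The scan timing rule.* It refers only to distance from menstruation.
- *The MRI analysis.* Age and mean framewise displacement are named as covariates, for the comparison of DOR patients with healthy controls. No adjustment for stimulation is stated for the longitudinal maps.

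**The case against.** The strongest reply is that the instruction on additional interventions already covers the gap. Its list is introduced as examples, and ovarian stimulation plainly could affect AFC, FSH and AMH. The two rules would then do different jobs: the exclusion screens plans at entry, and the instruction governs conduct during the trial. The inclusion criterion describes intent and does not authorise IVF before week 12. This reading is possible, and the sponsor may hold it. It does not rescue the 2-month figure, which would still enroll women whose plans conflict with the instruction.

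Other points stand in part:

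- **No effect is shown.** The article does not say how many women would start IVF, nor that stimulation would measurably change resting-state connectivity. Allocation is randomized, and there is no stated reason to expect uptake to differ between arms. This limits the point to uncovered time, and no bias is claimed.
- **The scans already vary in cycle phase.** This is true, but a stimulated cycle adds an external hormonal treatment to the natural variation that the design accepts.
- **Deferral has a cost.** These women want to conceive, have low reserve, may be up to 40, and half receive sham. The article itself mentions their urgent needs and expects that dropout may be higher. This is a good reason not to extend the exclusion to week 24, although the week-24 markers then remain exposed.
- **An article condenses the full protocol.** Fuller rules on concomitant treatment may exist there. The 2-month limit, however, is a stated figure that does not fit the stated schedule; it is not an omitted detail.

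**Conclusion.** The concern holds. The exclusion ends at least 22–25 days before the week-12 markers and the second scan, and no other stated rule clearly covers that time. The 22–25 days assume that the first session is on the day of enrollment; any wait adds to them day for day. The number of women affected, and the size and direction of any effect on the comparison of verum with sham, cannot be estimated from the article. Confidence that this matters in practice is medium, because the general instruction may have been meant to bar stimulation. It is an inexpensive improvement to the design, not a flaw that invalidates the trial.

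**What to change.** 1. **Exclusion criterion.** Replace the 2-month limit with: plans for IVF or ovarian stimulation before the week-12 assessments, including the second MRI, are complete. Tying the limit to the assessments and not to a number of days from enrollment also removes the dependence on when treatment starts.
2. **Instruction on additional interventions.** State that ovarian stimulation is among the barred interventions until those assessments are complete.

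Stopping at week 12 protects the scan and the post-treatment markers while keeping the deferral short.

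The cost is a wording change to one criterion and one instruction, slightly slower recruitment, and for some women about 3–4 weeks' longer wait for IVF (22–25 days, more if treatment starts well after enrollment). If the sponsor always meant the instruction to cover IVF, the change only records that intent.
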